## 7.5 Report of serious adverse events

To ensure patient safety, every SAE, regardless of suspected causality, occurring after the patient signs the informed consent and until 4 weeks after the patient has stopped study treatment must be reported to Novartis Safety Desk within 15 days of learning of its occurrence. Any SAEs experienced after this 4-week period should only be reported to Novartis Safety Desk if the investigator suspects a causal relationship to the study drug.

Recurrent episodes, complications, or progression of the initial SAE must be reported as follow-up to the original episode within 15 days of the investigator receiving the follow-up information. An SAE occurring at a different time interval or otherwise considered completely unrelated to a previously reported one should be reported separately as a new event.

Information about all SAEs is collected and recorded on the Serious Adverse Event Report Form. The investigator must assess and record the relationship of each SAE to each specific study drug (if there is more than one study drug), complete the SAE Report Form in English, and send the completed, signed form within 15 days to Novartis Safety Desk.

**7.6 Report of pregnancy**

To ensure patient safety, each pregnancy in a patient on study drug must be reported to Novartis. The pregnancy should be followed up to determine outcome, including spontaneous or voluntary termination, details of the birth, and the presence or absence of any birth defects, congenital abnormalities, or maternal and/or newborn complications.

Pregnancy should be recorded on a Clinical Trial Pregnancy Form and reported by the investigator to the local Novartis Safety Desk according to ‘SAE/IN, Pregnancy Reporting Procedures’. Pregnancy follow-up should be recorded on the same form and should include an assessment of the possible relationship to the Novartis study drug of any pregnancy outcome. Any SAE experienced during pregnancy must be reported on the SAE Report Form.

[figure not shown]

# 8. Data analysis

## 8.1 Analysis group

Data were summarized using descriptive statistics: frequency and percentage for categorical variables and mean ± SD for continuous variables. Differences in study participants' characteristics were compared across subgroups using chi-square tests or Fisher’s exact tests for categorical variables and independent t tests or Mann-Whitney’s U tests for continuous variables, as appropriate. To check for normal distribution, we used the Shapiro-Wilk’s test. Changes at end point from baseline were compared using an analysis of covariance (ANCOVA) model, with the use of the baseline score as a covariate. We used bar charts for data visualization. Intent to treat (ITT) and per protocol (PP) analyses were performed and the last observed carried forward (LOCF) method was used to impute missing values. P values lower than 0.05 were considered statistically significant. All statistical analyses were carried out using Statistical Package for Social Sciences 22.0 (SPSS Statistics for Windows 22.0, Armonk, NY, IBM Corp.) statistical software. All tests were two-tailed.

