**5.3. Sample size justification**

In order to detect the difference in means of 2.3 (assumed from Kumar et al, 2000 as the difference between patients treated with 6-12 mg/day rivastigmine with and without vascular risk factors) of ADAS-cog change from baseline to Week 24 between AD patients with WMC and AD patients without WMC when a two-group t-test with a 0.05 two-sided significance level is used, the sample sizes in the two groups are 81 in AD patients with WMC and 162 for AD patients without WMC (a total sample size of 243), assuming that the common standard deviation is 6.0 (Winblad et al, 2007; Erkinjuntiti et al, 2002) and the allocation ratio of 1:2. The method of sample size calculation is as follows:

[figure not shown]
,

[figure not shown]

[figure not shown]

[figure not shown]

[figure not shown]

[figure not shown]

[figure not shown]

When the drop-out rate is expected to be 20%, a total number of required will be **300** patients (**100** in AD with WMC and **200** in AD without WMC).

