**6.2.2 Subject assignment and prescribing and administering medication**

Patient subjects will be allocated to AD without white matter change group or AD with white matter change group at the baseline. All patients start on a 5-cm2 patch and their dose is increased to a 10-cm2 patch after 4 weeks. White matter changes will be defined by CREDOS protocol. Periventricular white matter (PWM) changes are classified into P1 (caps or rim <5 mm), P2 (5 mm <caps or rim <10 mm), P3 (10 mm <caps or rim). Likewise, deep white matter (DWM) ischemic lesions are classified into D1 (the longest diameter of DWM lesion <10 mm), D2 (10mm<DWM<25mm), and D3 (25mm <DWM). The patients would be divided into two groups according to combinations of PWM and DWM ischemic lesions: Group I (without or minimal white matter changes: D1P1,) and Group II (mild to moderate white matter changes: D1P2, D2P1, D1-P3, D2-P2, D2-P3, D3-P1, D3-P2).

| **Treatment Arm** | **# of Patients Entered Treatment** | **Type of Study Drug** | **Compound** | **Min Dose** | **Max Dose** | **Frequency** | **Admin. Route** |
| --- | --- | --- | --- | --- | --- | --- | --- |
| AD without WMC | 200 | Exelon patch | Rivastgmine | 5cm2 | 10cm2 | qd | PO |
|  |  |  |  |  |  |
| AD with WMC | 100 | Exelon patch | Rivastgmine | 5cm2 | 10cm2 | qd | PO |
|  |  |  |  |  |  |

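### The ANCOVA in section 8.1, on its natural reading, pools one residual variance over two MRI-defined groups planned 1:2, so its 5% level is not assured if the groups differ in spread

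*Protocol*

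**What the plan says.** Protocol section 8.1 fixes the comparison: "Changes at end point from baseline were compared using an analysis of covariance (ANCOVA) model", adjusted for the baseline score. It sets the decision rule ("P values lower than 0.05 were considered statistically significant", all tests two-tailed) and names SPSS 22.0. It provides a normality check (Shapiro-Wilk) but says nothing about equality of variance, a variance structure or a robust standard error.

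Section 5.3 plans the study on "a two-group t-test with a 0.05 two-sided significance level is used", "assuming that the common standard deviation is 6.0" "and the allocation ratio of 1:2". The result is that "the sample sizes in the two groups are 81 in AD patients with WMC and 162 for AD patients without WMC".

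Section 6.2.2 forms the groups from MRI ratings. Group I is the single class D1P1. The other is "Group II (mild to moderate white matter changes: D1P2, D2P1, D1-P3, D2-P2, D2-P3, D3-P1, D3-P2", which is seven combinations of deep and periventricular grades.

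**The concern.** An ordinary ANCOVA estimates one residual variance from all patients and uses it for the standard error of the group difference. In a randomised trial with truly no effect, both arms share one outcome distribution, so pooling is safe under the null. Here the groups are pre-existing patient classes. The mean change could be identical in both while the spread differs.

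Some difference in spread is plausible. Group II mixes seven lesion classes, and the rationale in section 4.1 is that vascular pathology modifies the response.

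Unequal spread would matter little with equal group sizes. With a 1:2 split, the larger group dominates the pooled variance while the smaller group dominates the true variance of the difference. If the smaller Group II varies more, the standard error is too small and the test rejects too often. If Group II varies less, the standard error is too large and power is lost. The p<0.05 rule for ADAS-Cog, any confidence interval from the same model, and the same analysis of the six secondary scales all depend on this.

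**Working it through.** **Inputs.** From section 5.3: difference 2.3, common SD 6.0, two-sided 0.05, ratio 1:2, evaluable 81 v 162. Power does not appear in the readable text, so 80% is assumed; 85% would need 92 in the smaller group and 90% would need 108, so only 80% fits. SD ratios between groups are assumptions throughout.

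**The plan's own figure.** Smaller group: n = (1 + 1/2) × (1.960 + 0.842)² × 6.0² / 2.3² = 1.5 × 7.85 × 36 / 5.29 = 80.1, rounded up to 81. The larger group is 162 and the total 243, as stated. Noncentral-t power at 81 v 162 is 80.1%. The sample size is not in error on its own assumptions.

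**Size of the pooled test when SDs differ.** Let Group I have SD 1 and Group II have SD r.

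- True variance of the difference: r²/81 + 1/162
- Pooled variance: s² = (80r² + 161)/241, giving s² × (1/81 + 1/162)
- True two-sided error: 2 × [1 − Φ(1.96 × pooled SE / true SE)]

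Worked case, r = 1.25: true variance = 1.5625/81 + 1/162 = 0.02546; s² = (125 + 161)/241 = 1.1867; pooled variance = 1.1867 × 0.01852 = 0.02198. The SE ratio is √(0.02198/0.02546) = 0.929, and the error is 2 × [1 − Φ(1.821)] = 6.9%.

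The analytic result was checked by simulating the ANCOVA with a baseline covariate at 81 v 162 (20,000 null runs per setting; Monte Carlo standard error near 5% is √(0.05 × 0.95/20,000), about 0.15 points).

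| Group II/Group I SD ratio | Group II SD if Group I is 6.0 | Pooled SE / true SE | Analytic error | Simulated, pooled | Simulated, HC3 |
|---|---|---|---|---|---|
| 0.8 | 4.8 | 1.076 | 3.5% | 3.3% | 4.7% |
| 1.0 | 6.0 | 1.000 | 5.0% | 4.9% | 4.8% |
| 1.07 | 6.43 | 0.98 | 5.5% | not run | not run |
| 1.25 | 7.5 | 0.929 | 6.9% | 6.5% | 4.7% |
| 1.5 | 9.0 | 0.879 | 8.5% | 8.7% | 5.0% |
| 2.0 | 12.0 | 0.816 | 11.0% | 11.3% | 5.1% |

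A nominal 95% interval has coverage of 100% minus the error: about 96.5%, 93.1% and 91.5% at ratios 0.8, 1.25 and 1.5. At 100 v 200 the analytic errors are the same to within 0.0001. At 121 v 121 the error stays at 5.0% at every ratio, so the 1:2 split is what creates the sensitivity.

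**What the seven classes could contribute.** If mean change varied across the Group II classes with SD 2.3 (as large as the whole planned difference), the Group II SD would be √(6.0² + 2.3²) = 6.43. That is the 1.07 row. To reach 7.5 by this route alone needs a between-class SD of √(7.5² − 6.0²) = 4.5; to reach 9.0 needs √(9.0² − 6.0²) = 6.7.

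**The case against.** The best counter-argument is that the protocol leaves the variance estimator open. Pooling is inferred from silence, and the choice of standard error is commonly left to a statistical analysis plan, which is not shown. This stands in part: the silence is not a defect in itself. However, section 8.1 already names the test, the threshold and the package, so a reader following it would run the default model.

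Second, the only SD in the documents is the common 6.0, and every distortion above rests on a ratio chosen for illustration. This stands in full. A reader might infer that the primary p-value fails its 5% level, or that a positive result would reflect spread rather than mean change. The documents support neither: if the common-SD assumption is true the level holds, and if Group II varies less the test is conservative.

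Third, pooling seven lesion classes cannot by itself plausibly produce the larger ratios. This also stands. A between-class SD of 2.3 gives only about 5.5%, so errors of 6.9% or 8.5% would need a further source of spread for which the documents give no figure.

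Fourth, a reader might extend the point to graphical error bars. Section 8.1 mentions bar charts only and specifies neither error bars nor confidence intervals, so the point reaches no further than an interval taken from the same model.

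Finally, the main hazard of MRI-defined groups is confounding, since the model adjusts only for the baseline score. That is correct, and a robust standard error does not address it.

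**Conclusion.** The point holds as a conditional weakness of minor weight. With an unrandomised 1:2 comparison and a pooled-variance ANCOVA, the nominal 5% level is not assured. For SD ratios of 0.8 to 1.25 the true error runs from about 3.5% to 6.9%, which is a modest distortion; it reaches 8.5% only at a ratio of 1.5. These figures assume approximate normality, the planned 81 v 162 split and the stated ratios, none of which the documents confirm or exclude for the two groups. No actual error in the p-value or the sample size is shown. The case for acting is that the protection is close to free.

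**What to change.** In section 8.1, keep the ANCOVA with the baseline score as covariate and add one sentence: the group difference, its 95% confidence interval and its p-value will be based on HC3 standard errors, or on a model with a separate residual variance for each group. Name one of the two in advance, and apply it to ADAS-Cog and to the six secondary scales.

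**Cost.** No extra patients or data are needed, and the 243 evaluable patients still follow from the plan's equal-SD assumption. If the variances are equal, simulated power falls by about 0.3 to 0.6 percentage points (for example, from 79.7% to 79.2%). If Group II varies less (SD 4.8 against 6.0), power rises from 87.2% to 90.0%. If Group II varies more (SD 7.5), the rejection rate at a difference of 2.3 falls from 71.5% to 66.0%, but the pooled figure there comes from a test running above its 5% level. The documents do not show how either option would be run in SPSS 22.0, so the software route must be confirmed before the sentence is fixed.

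Confounding between the MRI groups needs separate treatment.

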**1.2 Study design**

Investigator Initiative Trial, Multi-center, Prospective, Open-label

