**4.2 Primary objective**

To evaluate and compare the changes of cognitive function (as measured by ADAS-Cog) in the two group of patients with Alzheimer’s disease associated with and without white matter changes after rivastigmine patch therapy

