## 8.2 Subject demographic and background information

Data were summarized using descriptive statistics: frequency and percentage for categorical variables and mean ± SD for continuous variables. Differences in study participants' characteristics were compared across subgroups using chi-square tests or Fisher’s exact tests for categorical variables and independent t tests or Mann-Whitney’s U tests for continuous variables, as appropriate.

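### The primary contrast compares MRI-classified, non-randomised groups, but the only stated model adjusts for the baseline score alone, so age, sex and centre may confound it

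*Protocol*

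**What the plan says.** Section 1.2 describes the design as "Investigator Initiative Trial, Multi-center, Prospective, Open-label"; randomisation is not mentioned. Section 6.2.2 says "Patient subjects will be allocated to AD without white matter change group or AD with white matter change group at the baseline", but the rule that follows is a classification: "The patients would be divided into two groups according to combinations of PWM and DWM ischemic lesions". Group I is D1P1 and Group II is seven higher combinations. Section 6.2.1 gives both groups the same patch schedule.

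The primary objective (section 4.2) is "To evaluate and compare the changes of cognitive function (as measured by ADAS-Cog) in the two group of patients", so the between-group contrast is the main result. For its analysis, section 8.1 specifies "an analysis of covariance (ANCOVA) model, with the use of the baseline score as a covariate". Section 8.3.1, whose heading covers hypothesis, model and method, names the outcome and the time point and adds no covariate.

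Other patient characteristics appear only in a comparison of the groups: "Differences in study participants' characteristics were compared across subgroups using chi-square tests or Fisher’s exact tests for categorical variables", repeated in section 8.2. The text does not say what follows if they differ. No matching, stratification, propensity method or centre term is given.

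**The concern.** ANCOVA with the baseline score as sole covariate is a reasonable default when randomisation has balanced everything else in expectation. Here the grouping variable is a patient characteristic. Eligibility spans ages 50 to 90 and MMSE 10 to 24, and the study runs in several centres, so there is ample room for the two groups to differ in ways that also bear on 24-week change. Ratings are open-label, and section 7.3 asks for the same evaluator per patient where possible, so centre differences in rating or case mix can also enter the contrast.

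The protocol accepts the principle itself. Its background links vascular risk factors both to more white matter lesions and to a larger response to rivastigmine.

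At stake is the meaning of the primary p-value. A difference could be credited to white matter changes when part of it reflects age, sex or centre mix, or a true difference could be masked. A larger sample does not remove this bias.

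**Working it through.** **1. The plan's own figure.** Inputs from section 5.3: difference 2.3, SD 6.0, two-sided alpha 0.05, ratio 1:2. Power is not in the readable text (the formula is in figures); 80% is assumed.

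Smaller group = (1 + 1/2) × [6.0 × (1.960 + 0.842) / 2.3]² = 80.1, rounded up to 81. The larger group is 162 and the total 243, as stated. Power of 85% would give 276 and 90% would give 324, so 80% is the implied value. Dropout: 243 / 0.8 = 303.75, i.e. 304, against 300 stated, which is close enough. The sample size is not at fault; it simply treats the 2.3 points as free of confounding.

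**2. Evaluable numbers.** 300 × 0.8 = 240, i.e. 80 with and 160 without white matter changes. SE = 6.0 × √(1/80 + 1/160) = 0.822. Power for 2.3 by the noncentral t is 79.6%.

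**3. Effect of a residual bias (assumed, not from the protocol).** The noncentrality is bias / 0.822 when there is no true difference, and (2.3 − bias) / 0.822 when the bias works against a true 2.3.

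| Assumed bias (points) | Share of 2.3 | False-positive rate | Power for 2.3, bias opposing |
|---|---|---|---|
| 0 | 0% | 5.0% | 79.6% |
| 0.5 | 22% | 9.3% | 58.8% |
| 1.0 | 43% | 22.8% | 35.1% |

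**4. What could produce such a bias.** Bias = (group gap in a covariate, in SDs) × (partial correlation r with change, given baseline) × 6.0. A gap of 0.3 SD with r = 0.1 gives 0.18 point. A gap of 0.5 with r = 0.2 gives 0.60. A gap of 0.8 with r = 0.3 gives 1.44. The 0.5 to 1.0 range lies inside this grid, but the protocol supplies neither quantity.

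**5. Price of adjusting.** With one third and two thirds of patients in the groups, a covariate gap of g SDs multiplies the variance of the group effect by 1 + g² × (1/3)(2/3). If the covariates explain a share v of the residual variance, SE = 0.822 × √[(1 − v) × (1 + 2g²/9)].

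| Gap g | Variance factor | Power, v = 0 | Power, v = 10% |
|---|---|---|---|
| 0.3 | 1.020 | 78.8% | 82.9% |
| 0.5 | 1.056 | 77.5% | 81.6% |
| 0.8 | 1.142 | 74.2% | 78.5% |

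Adjusted power is therefore about 74%-83%, against 79.6% for the unadjusted t-test.

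**The case against.** The best case for the plan has four parts.

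- **No evidence of imbalance.** The protocol reports no group difference in age, sex or centre and no relation of these to ADAS-Cog change. A reader might infer that they do confound the result; the text supports only that they may. The bias range is assumed and its sign is unknown. This stands.
- **Severity is in the model.** A reader might infer that disease stage is unadjusted. Baseline ADAS-Cog is itself a severity measure, so only severity that it misses remains. Further scales such as CDR-SB or MMSE may themselves be affected by white matter lesions, so putting them in the primary model could remove part of the contrast of interest. This stands and shapes the fix.
- **Extra covariates can wait for an analysis plan.** The text does not say that the baseline score is the only covariate permitted, and it is silent on what follows an imbalance. This stands only in part: the protocol does not merely leave the model open. It names a model and a covariate, and 8.3.1 adds nothing. Followed as written, that model does not suit a non-randomised comparison.
- **Adjustment has a price.** A reader might expect covariates to raise power: with 10% of variance explained, SD 6.0 × √0.9 gives 83.6%. That requires covariates unrelated to group, whereas confounding presupposes that they are related to it. The gain cannot be claimed.

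**Conclusion.** The point holds in a limited form. The groups are observational, and the stated primary model adjusts for the baseline score alone, which leaves the main contrast open to confounding by age, sex and centre. No imbalance is documented, so the size is conditional. A residual bias of 0.5 to 1.0 point, with 80 and 160 evaluable patients and SD 6.0, would give a false-positive rate of about 9%-23% instead of 5%, or power of about 59%-35% instead of 80% if it runs the other way.

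A reader might also infer that an adjusted model would show whether the drug works better in patients with white matter changes. The design does not support that. Both groups receive the same patch and there is no untreated comparator, so adjustment cannot separate drug response from natural progression.

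**What to change.** In sections 8.1 and 8.3.1, state the primary analysis as ANCOVA of week-24 ADAS-Cog change on white matter group, baseline ADAS-Cog, age, sex and centre (fixed or random effect). Say that these covariates are fixed in advance and are not chosen from the section 8.2 tests, since selection on those p-values would make the primary analysis data-driven.

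Keep the baseline-only model as a secondary analysis. Add sensitivity models with baseline CDR-SB or MMSE and with vascular risk factors, and give the reason for keeping them out of the primary model: they may lie on the pathway from white matter lesions to outcome. Word the conclusion as an association between white matter group and change under treatment.

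The cost is a paragraph of text and some precision: power of about 74%-83% for assumed gaps of 0.3-0.8 SD and 0-10% of variance explained. The readable text does not give the number of centres, so the degrees of freedom that a fixed centre term would use cannot be stated. Little or no new data collection should be needed: age and sex are eligibility items, section 7.1 lists demographic data and medical history, and Table 1 has MMSE and CDR-SB at baseline.

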**8.3 Analysis of primary objective**

### 8.3.1 Evaluation variables statistical hypothesis, model and method analysis

Efficacy measures were assessed at baseline and on week 24. Primary outcome was the change from baseline on the Alzheimer’s Disease Assessment Scale-Cognitive subscale on week 24 (ADAS-Cog).

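### With no ADAS-Cog scheduled between baseline and Visit 5, LOCF enters zero change for dropouts without an exit test and can treat an early exit score as the week-24 value.

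*Protocol*

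**What the plan says.** Section 8.1 of the protocol plans intent-to-treat and per-protocol analyses, an ANCOVA of change with the baseline score as covariate, and a single rule for missing data: "the last observed carried forward (LOCF) method was used to impute missing values".

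Section 8.3.1 states "Efficacy measures were assessed at baseline and on week 24" and makes the week-24 change in ADAS-Cog the primary outcome. Table 1 in section 7 agrees. ADAS-Cog is marked at Visit 2 (Day 0) and Visit 5, with nothing at the 4-week or 12-week visit. The Visit 5 column covers 24 weeks or early termination.

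On early leavers the protocol says three things:

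- Section 7, general text: patients dropped after baseline return promptly for all final-visit assessments.
- Section 6.2.6, and the paragraph on treatment visits in section 7: patients who stop treatment early are assessed at the end of week 24.
- Section 6.2.5: patients unwilling to attend, or lost to follow-up, may be counted as dropouts. For those who stop attending without explanation, only a telephone conversation is asked for.

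Section 5.3 sizes the trial for a difference of 2.3 with SD 6.0 and then allows for dropout: "When the drop-out rate is expected to be 20"%.

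**The concern.** LOCF needs an intermediate score to carry, and this schedule provides none. What it does depends on the type of early leaver:

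- **No post-baseline test.** The last observation is the baseline, so the imputed change is exactly zero.
- **Tested promptly on leaving.** A score from an earlier week stands in for week 24. A patient who leaves soon after the week-4 patch step would be scored after little treatment.
- **Tested at week 24.** Nothing is missing.

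The first two values do not estimate the week-24 change that section 8.3.1 defines. If zeros are entered equally often in both groups, the difference shrinks. If not, the imputation itself creates or hides a difference. The groups are formed from MRI findings (section 6.2.2) and not by randomisation, so nothing in the design equalises dropout between them.

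**Working it through.** **Inputs from section 5.3.** "In order to detect the difference in means of 2.3"; "assuming that the common standard deviation is 6.0"; "two-group t-test with a 0.05 two-sided significance level is used"; "the allocation ratio of 1:2" (with : without white matter change); 20% dropout; 100 and 200 enrolled. Power does not appear in the readable text because the formula images are not shown, so 80% is inferred.

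**Step 1: the plan's own figure.** For the smaller group,

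n = (1.96 + 0.8416)² × 6.0² × (1 + 1/2) / 2.3² = 80.1, rounded up to 81.

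This gives 81 and 162, total 243, as stated. Dividing 243 by 0.80 gives 304, close to the stated 300.

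**Step 2: effect of entering zeros, equal in both groups.** Let q be the share of dropouts with no post-baseline ADAS-Cog. The documents give no value, so q is varied. The fraction entered as zero is f = 0.20 × q. All other patients, including those with exit scores, are assumed to show the full effect. Then:

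- expected difference = (1 − f) × 2.3, so bias b = −f × 2.3
- variance in a group with mean change m = (1 − f) × 36 + f(1 − f) × m²
- SE = √(V₁/100 + V₂/200)
- coverage of 2.3 = Φ(1.96 − b/SE) − Φ(−1.96 − b/SE)

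SE and coverage are shown for mean changes of 2.3 (with) and 0 (without). Power is shown over assumed mean changes of −2.3 to +2 in the group without white matter change (positive = improvement).

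| q | f | Difference | Bias | SE | Coverage of 2.3 | Power |
|---|---|---|---|---|---|---|
| 0 | 0 | 2.30 | 0 | 0.735 | 95% | 88% |
| 0.25 | 0.05 | 2.19 | −0.115 | 0.718 | 94.7% | 86% |
| 0.50 | 0.10 | 2.07 | −0.23 | 0.70 | 93.8% | 83–84% |
| 1 | 0.20 | 1.84 | −0.46 | 0.66 | 89% | 77–80% |

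Worked line for q = 1: V₁ = 0.8 × 36 + 0.16 × 2.3² = 29.65 and V₂ = 28.8, so SE = √(0.2965 + 0.144) = 0.664. Then b/SE = −0.693, and coverage = Φ(2.65) − Φ(−1.27) = 0.996 − 0.103 = 0.89.

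The SE in each line is the correct sampling SE of the LOCF estimate. The loss of coverage therefore comes from b alone.

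**Step 3: unequal shares entered as zero (illustration, all inputs assumed).** Take no true difference, a common mean change m, and 30% against 15% entered as zero. The spurious difference is m × (0.15 − 0.30).

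- |m| = 2: 0.30 points in size. V₁ = 0.70 × 36 + 0.21 × 4 = 26.04, V₂ = 0.85 × 36 + 0.1275 × 4 = 31.11, SE = 0.645, false-positive rate about 7.5%.
- |m| = 4: 0.60 points in size. V₁ = 28.56, V₂ = 32.64, SE = 0.670, false-positive rate about 15%.

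The sign follows the sign of m and which group has more zeros. If half of those dropouts had an unbiased exit score (15% against 7.5% as zero), the rates would be about 5.5% and 7.1%.

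All results use a normal approximation on the change score and do not model the ANCOVA covariate.

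**The case against.** The strongest reply is that the protocol does provide for dropouts. Visit 5 doubles as an early-termination visit, and section 7 asks early leavers to return for every final assessment. That stands. A reader might infer that LOCF mostly carries baseline forward, or that about 60 of 300 patients (20%) would be entered as zero. The documents do not support either: 60 is a ceiling, reached only if every dropout misses the exit test, and no attendance rate is given. Patients tested at week 24 under section 6.2.6 have nothing imputed.

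The cost under equal dropout is also modest. An analysis of the 80 and 160 completers would have about 80% power, so even the worst line in the table loses at most about 3 points against it.

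A reader might also blame the under-coverage on a standard error made too small by treating zeros as data. In this calculation it is bias.

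The 30% against 15% scenario is an assumption. Both groups follow the same patch schedule, and nothing in the documents predicts such a gap.

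Finally, imputation detail and sensitivity analyses usually belong in an SAP, which is not shown. Their absence from the protocol is not the fault here. The fault is that the protocol itself names LOCF. It is also fair to say that, for patients with no exit score, imputing from baseline variables adds little to an observed-case ANCOVA on the same variables. The gain is in removing the zeros and in using exit scores with their dates.

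**Conclusion.** The concern holds in a limited form. The stated rule does not estimate the week-24 change for dropouts without an exit test, or for those whose early exit score is carried forward. At the plan's 20% dropout in both groups, the design difference of 2.3 shrinks to between 2.19 and 1.84 as the untested share of dropouts goes from 25% to 100%, and coverage falls from about 94.7% to 89%. These shares are assumed, and off-time exit scores are treated as unbiased, so that second error is not in the figures. Under unequal shares the direction of bias is not fixed; its size in Step 3 only illustrates what could happen.

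The conflict over when early leavers are tested is part of the same defect, because it decides whether LOCF carries an early score or has nothing to impute.

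Severity: should be fixed. The unknown attendance at exit tests and the small loss under equal dropout do not support a stronger grade.

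**What to change.** In section 8.1, replace LOCF as the primary method. Apply the planned baseline-adjusted ANCOVA to week-24 ADAS-Cog, with missing week-24 scores multiply imputed within white matter group from baseline measures (such as ADAS-Cog, MMSE, CDR-SB and age) and any exit ADAS-Cog with its date. Keep LOCF only as a sensitivity analysis, beside a delta-adjusted analysis that varies the assumption about patients without a week-24 score.

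Reconcile sections 6.2.6 and 7 on whether early leavers are assessed promptly on leaving or at the end of week 24, and record the date of every exit test.

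The cost is wording, some extra programming and a somewhat wider interval. No new data are needed.
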